**Exploratory endpoints:**

The vaccine efficacy of recombinant COVID-19 vaccine (CHO cells) against COVID-19, severe cases and deaths after 14 days following sequential vaccination in population aged 18 years and above.

# **Clinical Trial Protocol**

## **Sequential Immunization of Recombinant COVID-19 vaccine (CHO cells) and Inactivated COVID-19 vaccine (Vero cells) in Population Aged 18 years and above**

### **1. INTRODUCTION**

The recombinant COVID-19 vaccine (CHO cell) developed by Sinopharm CNBG National Vaccine & Serum Institute (NVI) and Lanzhou Institute of Biological Products Co., Ltd. (LBP) affiliated to China National Biotec Group Co., Ltd (CNBG) is used to prevent the diseases caused by SARS-CoV-2. After being reviewed by National Medical Products Administration (NMPA) in accordance with *Drug Administration Law of the People's Republic of China*, *Vaccine Administration Law of the People's Republic of China* and *Provisions for Drug Registration*, it has been approved for Phase I/II clinical study in China, and the data obtained from the Phase I/II clinical trial in population aged 18 years and above completed showed good safety profile.

In this project, a randomized, blinded, positive control method will be used to evaluate the safety and immunogenicity of sequential vaccination of recombinant COVID-19 vaccine (CHO cells) in healthy population aged 18 years and above. This study was approved by the Ministry of Health of UAE.

### **2. BACKGROUND AND PRINCIPLE**

#### **2.1 Background of disease**

According to WHO data, as of July 23, 2021, there were 194,595,271 confirmed cases and 4,165,733 deaths due to COVID-19, with a mortality rate of 2.1%. The infection sources of COVID-19 are mainly SARS-CoV-2 infected patients and asymptomatic infected persons, but it is found that patients in incubation period are also contagious, and they are highly contagious within 5 days after onset. SARS-CoV-2 is mainly transmitted through respiratory droplets and close contact, which may be transmitted by aerosol. Contact with virus contaminated articles can also cause infection. Because SARS-CoV-2 can be isolated from patients' feces and urine, environmental pollution caused by feces and urine can also cause aerosol or contact transmission.

People are generally susceptible, and they can get infection in all ages. People can get certain immunity after infection or vaccination with COVID-19 vaccine, but the duration is not clear. Based on the current epidemiological investigation, the incubation period of virus is generally 1 ~ 14 days, mostly 3 ~ 7 days, and the incubation period of very few cases can reach 24 days.

The main clinical symptoms of COVID-19 are fever, dry cough and fatigue, and the first symptoms of some patients are loss of smell and taste. A few patients are accompanied by nasal congestion, runny nose, sore throat, muscle pain and diarrhea. According to clinical symptoms, it can be divided into four categories: mild, moderate, severe and critical. Severe patients often have dyspnea and/or hypoxemia one week after onset, and severe patients can rapidly progress to acute respiratory distress syndrome, septic shock, metabolic acidosis, coagulation dysfunction and multiple organ failure. Very few patients may also have central nervous system involvement and acrovascular necrosis. It is worth noting that severe and critical patients may have moderate to low fever or even no obvious fever during the course of disease. Mild patients may show low fever, slight fatigue, smell and taste disorders, etc., without pneumonia. A few patients have no obvious clinical symptoms after being infected with SARS-CoV-2. According to the current cases, most patients have a good prognosis, while a few patients are in critical condition. The prognosis of the elderly and those with chronic basic diseases is poor. The clinical process of pregnant women with COVID-19 is similar to that of patients of the same age. Children's cases have relatively mild symptoms.

## **2.2. Pathogenic background**

SARS-CoV-2 belongs to  $\beta$  coronavirus. Under cryoelectron microscope, it is approximately spherical particles with variable diameter, mainly around 100nm. SARS-CovV-2 contains dense virus matrix, surrounded by lipid bilayer, and its outer surface protrudes. It is an enveloped virus, which is composed of non-segmental positive-sense single-stranded RNA and protein. It belongs to Orthocoronavirinae and is widely distributed in humans and other mammals.

The genome of SARS-CoV-2 strain is 29.9 kb long and encodes 9860 amino acids. SARS-CoV-2 has four main structural proteins, known as spike protein (S), membrane protein (M), envelope protein (E) and nucleocapsid protein (N), as well as several helper proteins. S, M and E proteins constitute the viral envelope and are the main surface antigens of virus-induced immune response. S protein is a transmembrane glycoprotein with a molecular weight of about 150kDa, which is divided into two subunits, namely S1 and S2, by Furin protease of host cells. S1 contains one RBD, which is responsible for determining the cell targeting between host cells and virus receptor binding domains; As a membrane fusion subunit, S2 can mediate virus to fuse with host

cells. M protein plays an important role in determining the shape of viral envelope. It can bind with other structural proteins, and binding with N protein helps to stabilize nucleocapsid and promote the assembly of virus. E protein plays an important role in the process of virus production and maturation. N protein is located in the core of virus and combines with viral RNA to form nucleocapsid. N protein has a highly conserved sequence, and it participates in virus replication and infection of host cells.

The binding of spike protein (S protein) with angiotensin converting enzyme 2 (ACE2) protein is essential for SARS-CoV-2 infecting human cells. After fusion, transmembrane protein serine 2 (TMPRSS2), which exists on the surface of host cells, scavenges ACE2 and activates S protein. Activation of the S protein causes a conformational change and allows the virus to enter the host cell. The affinity of S protein of SARS-CoV-2 with ACE2 is 10 to 20 times that of SARS virus, which may be the reason of strong transmission of COVID-19. ACE2 expressed in respiratory epithelial cells and type II alveolar cells of lung is the receptor of SARS-CoV-2 entering host cells. Besides lung, ACE2 is also distributed in intestinal epithelial cells of ileum and colon, vascular smooth muscle cells, proximal tubular epithelial cells of kidney, urinary tract epithelial cells of bladder and testis. Therefore, COVID-19 patients will not only have respiratory diseases, but also have heart, kidney, and digestive system diseases. ACE2 expression in vascular intima can damage endothelial cells and lead to the risk of thrombotic events. In addition, the immune system releases a large number of cytokines to viral infection sites or secondary infection, which can induce cytokine storm and septicemia symptoms.

In addition, coronavirus is sensitive to ultraviolet rays and heat. For 30 minutes at 56 °C, ether, 75% ethanol, chlorine-containing disinfectant, peracetic acid and chloroform can effectively inactivate the virus, but chlorhexidine cannot effectively inactivate the virus.

### **2.3. Vaccine background**

As of 26 March 2021, according to the statistics from World Health Organization (WHO), there are 267 COVID-19 vaccine projects in active research and development around the world, with diversified technical routes, mainly including inactivated vaccines, recombinant protein vaccines, viral vector vaccines and nucleic acid vaccines. There are 83 candidate vaccines in clinical stage, including 27 recombinant protein vaccines, among which NVX-CoV2373 developed by Novavax is in Phase III stage, recombinant protein vaccine developed by Zhifei Bio has been authorized for emergency use in China, and others are in Phase I/II study. And four inactivated vaccines, four recombinant viral vector vaccines and four nucleic acid vaccines are in

Phase III clinical trial.

### **2.3.1 Inactivated vaccine**

Inactivated vaccine is made from virus that has been grown in cell culture and have been lose its pathogenicity by physical or chemical method, but only retain its antigenicity. As a traditional vaccine preparation method, the process is mature. At present, there are 22 inactivated vaccines under research around the world, of which 11 are in clinical stage. The inactivated vaccines of Sinopharm CNBG Wuhan Institute of Biological Products and Beijing Institute of Biological Products have carried out Phase III clinical study in UAE, and have been approved for conditional marketing in 8 countries including UAE and China, and authorized emergency use in 86 countries. The published clinical results showed good safety and efficacy. The seroconversion rate of antibody in two-dose immunization schedule is 100%, and the vaccine efficacy is 79%. Phase III clinical results of inactivated vaccine CoronaVac of Sinovac Research & Development Co., Ltd. in Brazil, Turkey and Indonesia showed that the vaccine efficacy is higher than 50% efficacy threshold set by the World Health Organization, and it has been approved for conditional marketing in China and authorized for emergency use in many countries and regions.

### **2.3. 2 Recombinant Protein Vaccine**

Compared with other types of vaccines, recombinant protein vaccines are one of the key directions of research and development in novel vaccines due to its significant advantages in safety and low cost. At present, 96 COVID-19 recombinant protein vaccine candidates are under development, and 27 of them are at clinical evaluation stage.

The recombinant nanoparticle vaccine NVX-COV2373 developed by NOVAVAX consists of full-length SARS-CoV-2 spike glycoprotein trimer and MATRIX-MTM adjuvant. The latest published phase III clinical interim results from UK showed that among 15,000 volunteers aged 18-84 years (27% volunteers are over 65 years old), the overall efficacy was 89.3% (56 cases in the placebo group and 6 cases in the vaccine group), and the efficacy against B.1.1.7 variant was 85.6%. According to the clinical data from Phase IIB in South Africa, among the 4,400 volunteers (6% were HIV positive), the efficacy of NVX-COV2373 in HIV negative population was 60% (29 cases in placebo group and 15 cases in vaccine group), and the efficacy of 49.4% if HIV positive population was included. Among COVID-19 infections, 90% cases were 501Y.V2 variants.

In the research pipeline of China, Zifei's recombinant protein vaccine (CHO cell) contains of SARS-COV-2 S protein receptor binding domain (RBD) unique dimer as antigen, adjuvanted by traditional adjuvant, and has been authorized for emergence use in China. The published clinical phase II data showed that among 900 volunteers, the seroconversion rate of neutralizing antibody

was 97% and the titer of neutralizing antibody (GMT) was 102.5 (CPE test method), which was twice as high as the antibody in the convalescent serum. In terms of safety, no serious adverse events related to vaccines were observed. In addition, Clover Biopharmaceuticals' recombinant protein vaccine is also in Phase II/III clinical trial.

### **2.3. 3 Recombinant Viral Vector Vaccines**

Viral vector vaccine uses replicative or non-replicative viruses as vectors, recombines specific antigen gene fragments into the vector genome, and delivery them into host cells, and induces expression and induces corresponding immune response. Currently, there are 19 recombinant viral vector vaccines in clinical stage, of which 3 are in the process of Phase III clinical trial.

AZD1222 (CHADOX1 NCOV-19), jointly developed by Oxford University and AstraZeneca, uses replication-deficient chimpanzee adenovirus CHADOX1 as vector to expresses SARS-CoV-2 S protein, and has been authorized for emergency use in UK, Brazil and other countries and regions. Recently, the European Union approved the conditional marketing of the vaccine for immunization in population aged 18 years and above, and the efficacy was evaluated as 59.5%. Previously, the Phase III clinical results published by AstraZeneca from the UK and Brazil trials showed that the average vaccine efficacy was 70% (vaccine efficacy of 90% with 1.5 doses, N=2741; vaccine efficacy of 62% with full doses, N=11636).

AD5-NCOV, jointly developed by Academy of Military Sciences and CanSino, uses replication-defective human adenovirus type 5 as vector to expresses SARS-CoV-2 S protein, and has been approved for conditional marketing in China. The published phase II clinical data showed that 28 days after single dose inoculation, the titers of RBD specific antibody in high dose group ( $1 \times 10^{11}$ ) and low dose group ( $5 \times 10^{10}$ ) were 656.5 and 571.0, respectively. The titer of neutralizing antibody was 19.5 and 18.3 respectively, and the seroconversion rate of neutralizing antibody was 59% and 47% respectively.

### **2.3. 4 NUCLEIC ACID VACCINE**

Nucleic acid vaccines introduce DNA or mRNA encoding specific antigens into human cells, express corresponding antigen proteins, and induce immune response. Currently, there are 60 nucleic acid vaccines in active research and development, and 21 vaccines in clinical stage, including 11 mRNA vaccines and 10 DNA vaccines.

mRNA-1273 developed by MODERNA, uses liposome nanoparticles (LNP) delivery system, and encodes SARS-CoV-2 S-2P antigen (composed of SARS-CoV-2 glycoprotein and complete S1-S2 cleavage site). mRNA-1273 has been granted emergency use authorization by FDA in mid-

December 2020. The results of a Phase III clinical trial showed that among more than 30,000 subjects who received vaccine or placebo randomly, the vaccine efficacy was 94.1% (185 cases in the placebo group versus 11 cases in the vaccine group), and there was zero case of severe COVID-19 in the vaccine group.

mRNA vaccines BNT162B1 and BNT162B2 jointly developed by BIONTECH, Pfizer and Fosun Pharma uses LNP delivery system and encode SARS-CoV-2 S protein RBD trimer and full-length S protein respectively. BNT162B2 has been authorized for emergency use in the United States, the European Union and other regions, and is the first COVID-19 vaccine authorized by WHO for emergency use listing. The previously published Phase III clinical trial data showed that among 44,000 subjects, vaccine efficacy after two doses of vaccine was 95% (162 cases in the placebo group and 8 cases in the vaccine group).

### **3. STUDY OBJECTIVE**

To evaluate the safety and immunogenicity of sequential vaccination of recombinant COVID-19 vaccine (CHO cells) developed by Sinopharm CNBG National Vaccine & Serum Institute in healthy population aged 18 years and above.

#### **3.1. Primary Objectives**

To evaluate the immunogenicity of recombinant COVID-19 vaccine (CHO cells) and inactivated COVID-19 vaccine (Vero cells) 14 days after sequential vaccination of one dose in population  $\geq 18$  years of age.

To evaluate the immunogenicity of recombinant COVID-19 vaccine (CHO cells) and inactivated COVID-19 vaccine (Vero cells) 28 days after sequential vaccination of one dose in population  $\geq 18$  years of age.

#### **3.2. Secondary Objectives**

To evaluate the safety of recombinant COVID-19 vaccine (CHO cells) and inactivated COVID-19 vaccine (Vero cells) 28 days after sequential vaccination of one dose in population  $\geq 18$  years of age.

To evaluate the optimal immunization schedule of sequential vaccination of recombinant COVID-19 vaccine (CHO cells) in population  $\geq 18$  years of age.

To evaluate the immune persistence of sequential vaccination of recombinant COVID-19 vaccine (CHO cells) and inactivated COVID-19 vaccine (Vero cells) in population  $\geq 18$  years of

age.

### 3.3 Exploratory Objectives

To evaluate the vaccine efficacy of recombinant COVID-19 vaccine (CHO cells) against COVID-19, especially severe cases, and deaths, after 14 days following sequential vaccination at different schedules.

To evaluate the vaccine efficacy of recombinant COVID-19 vaccine (CHO cells) against different variants after 14 days following sequential vaccination at different schedules.

## 4. STUDY DESIGN

### 4.1. Trial Description

This clinical trial is a randomized, blinded and positive controlled design.

### 4.2. Procedures and Methodology

#### Sample size:

Total of 1,800 healthy subjects aged 18 years and above who have been vaccinated with 2 doses of inactivated COVID-19 vaccine, will be enrolled, and randomly assigned to experimental group and control group in a 1:1 ratio., with 300 subjects in each sequential group.

#### Immunization Schedule:

The subjects who have been vaccinated with two doses of inactivated COVID-19 vaccine according to the immunization schedule of 0 and 21 (+7) days will receive sequential vaccination of one dose of recombinant COVID-19 vaccine (CHO cells) or inactivated COVID-19 Vaccine at different schedules of 1-3 months, 4-6 months and  $\geq 6$  months.

**Route of Administration:** lateral deltoid muscle of upper arm, intramuscular injection

#### Safety Observation:

The subjects will be observed at the study site for 30 minutes after vaccination, and local and systemic adverse events will be collected. Within 0-30 days after vaccination, the local and systemic reactions of the subjects will be actively followed up and recorded on the vaccination diary card.

Serious adverse events (SAEs) need to be monitored from the first dose of vaccination and up to 6 months following the full course of immunization.

#### Immunogenicity Observation:

Blood samples of all the subjects will be collected before the vaccination of sequential dose and 14 days, 28 days, 3 months, 6 months, 9 months and 12 months after sequential vaccination for detection of neutralizing antibodies and anti-protein specific IgG antibodies.

Collect 12.5ml blood samples of all the subjects and separate serum. Neutralizing antibody will be determined by microdose cytopathogenic efficiency (CPE) assay and specific IgG antibody will be tested by enzyme-linked immunosorbent assay (ELISA).

Time points of blood sample collection is described in Table 1 Sample Size and Procedures of Clinical Trial.

**Table 1 Sample size and Procedures of Clinical Trial**

| Sequential Vaccination Time of Recombinant Vaccine | Booster Immunization | Sequential Vaccine Group | Sample Size | Safety                                                                                                                                                                                         | Blood Collection Time Point                                                                                                             |
|-----------------------------------------------------------|-----------------------------|---------------------------------|--------------------|-------------------------------------------------------------------------------------------------------------------------------------------------------------------------------------------------------|------------------------------------------------------------------------------------------------------------------------------------------------|
| 1-3 months after 2 doses                                  | 31-90 days                  | Recombinant Vaccine             | 300                | Collected solicited AEs within 0-7 days and non-solicited AEs within 8-30 days after immunization with sequential booster dose, and SAEs up to 6 months following immunization with the booster dose. | Before the sequential dose
①, 14 days②, 28 days ③, 3 months ④, 6 months ⑤, 9 months ⑥, 12 months ⑦after sequential vaccination of one dose. |
|                                                           |                             | Inactivated Vaccine             | 300                |                                                                                                                                                                                                       |                                                                                                                                                |
| 4-6 months after 2 doses                                  | 91-180 days                 | Recombinant Vaccine             | 300                |                                                                                                                                                                                                       |                                                                                                                                                |
|                                                           |                             | Inactivated Vaccine             | 300                |                                                                                                                                                                                                       |                                                                                                                                                |
| ≥ 6 months after 2 doses                                  | ≥ 181 days                  | Recombinant Vaccine             | 300                |                                                                                                                                                                                                       |                                                                                                                                                |
|                                                           |                             | Inactivated Vaccine             | 300                |                                                                                                                                                                                                       |                                                                                                                                                |
| Total sample size                                         |                             |                                 | 1800        |                                                                                                                                                                                                       |                                                                                                                                                |

Note:

1) Blood collection window at 14 days, 28 days is +10 days, blood collection window at 3M, 6M, 9M, 12M is +30 days.

2) If the blood sample test results show that the antibody level is too low after the full immunization, blood collections at subsequent time points will not be carried out.

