| 
Note:
 
1) Blood collection window at 14 days, 28 days is +10 days, blood collection window at 3M, 6M, 9M, 12M is +30 days.
 
2) If the blood sample test results show that the antibody level is too low after the full immunization, blood collection at subsequent time points will not be carried out.
 |                                                                                                                                                                                                                                                                                                                                                                                                                                                                                                                                                                                                                                                                                                                                                                                                                                                                                                                                                                                                                                                                                                                                                                                                                                                                                                                                                                                                                  |  |      |  |                          |

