#### **4.3.3 Immune Persistence Endpoints:**

GMT of anti-SARS-CoV-2 neutralizing antibody and IgG antibody, the proportions of neutralizing antibody titered  $\geq 1:16$ ,  $\geq 1:32$  and  $\geq 1:64$  at 3 months, 6 months, 9 months and 12 months after full course of immunization,

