**Blood Sample Collection after Immunization**

About 12.5 ml of venous blood was collected from all subjects at 14 days, 28 days, 3 months, 6 months, 9 months and 12 months after immunization, and the serum was separated within 24 hours and packed into 2 tubes (each tube is not less than 0.5 ml), which were stored at -20 °C and below for immunogenicity neutralizing antibody detection.

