#### **10.2 Analysis Set**

Full Analysis Set (FAS): It includes all randomized participants who follow ITT principle, receive 1 dose of vaccine, and have valid immunogenicity data before the first dose.

Per-Protocol Set (PPS): It includes all participants who do not violate the inclusion criteria/exclusion criteria, receive 1 dose of vaccine, and have both valid pre- and post-vaccination immunogenicity data. PPS will be defined for immunogenicity evaluations 14 and 28 days after sequential vaccination, respectively.

Immunogenicity Persistence Set (IPS): It include the participants who are collected

with blood samples at each time point for immunogenicity persistence evaluation and with valid antibody data. Define the IPS for immunogenicity for 3, 6, 9, 12, 18 and 24 months after sequential immunization respectively.

Safety Set (SS): It includes all participants who receive one dose of vaccination.

In immunogenicity analysis, the participant who takes the vaccine erroneously will be included as randomized, and the safety data will be analyzed as treated.

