#### **10.7 Handling of Missing Data**

In FAS immunogenicity analysis, LOCF (Last Observation Carried Forward) method will be used to impute the missing values in antibody data after vaccination. And other

immunogenicity endpoints will be derived from the imputed data. The missing data in safety and immunogenicity persistence evaluation will be not imputed.

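### The undefined low-antibody stop in Table 1 Note 2 contradicts the all-subject blood schedule and makes the 3 to 12 month persistence results either selected or absent

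*Protocol*

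**What the plan says.** Persistence of both boosters is a secondary objective (section 3.2). Section 4.3.3 gives it its own endpoints: neutralizing and IgG GMTs, and the proportions with neutralizing titre at or above 1:16, 1:32 and 1:64, "at 3 months, 6 months, 9 months and 12 months after full course of immunization".

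The protocol gives two instructions on who is bled at those visits.

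- Section 7.4 has blood "collected from all subjects at 14 days, 28 days, 3 months, 6 months, 9 months and 12 months", with no condition. The immunogenicity paragraphs of the synopsis and section 4.2 say the same, the sample-numbering rule in section 7.4 allots a number to every draw, and Table 4 ticks both antibody tests at V4 to V9.
- Note 2 to Table 1 makes later draws conditional: if the "antibody level is too low after the full immunization, blood collections at subsequent time points will not be carried out". The synopsis repeats it almost word for word ("antibody level is too low after the full immunization, blood collection at subsequent time points will not be carried out").

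Two analysis rules determine what a missed draw does. Under section 10.2 the Immunogenicity Persistence Set (IPS) takes participants "with blood samples at each time point for immunogenicity persistence evaluation and with valid antibody data". Section 10.7 adds: "The missing data in safety and immunogenicity persistence evaluation will be not imputed".

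Section 10.2 also says: "Define the IPS for immunogenicity for 3, 6, 9, 12, 18 and 24 months after sequential immunization respectively". No blood is scheduled after 12 months.

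**The concern.** Whether a later sample exists depends on the quantity being measured. The low titres at 6, 9 and 12 months are what the GMT and the threshold proportions are meant to capture, and the note removes people because they were already low. With an IPS built from available samples and no imputation, each reported figure describes those who were above some unstated level earlier, not those who were randomized and boosted.

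The selection need not be equal in the two arms. The arm with lower titres at the deciding visit loses more of its low responders, so its reported GMT is raised more and the two vaccines look more alike than they are.

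If the note is meant for a whole group, no one is selected within a group, but that group's later time points do not exist and there is nothing to compare with the other arm.

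On either reading, sites hold two instructions that cannot both be followed, and blood not taken cannot be recovered at analysis.

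**Working it through.** **Inputs.** From the protocol: log10 SD 0.7 (section 10.1), the 1:16 threshold (section 4.3.3), and the IPS and no-imputation rules. Assumed, because the protocol gives no figure: earlier-visit GMT 32 or 64, a two-fold fall to the next visit, correlation ρ = 0.8 between visits, and a cut-off of 1:4 or 1:16 applied per subject at the earlier visit.

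**The plan's own figure.** No stated number is disputed; this only confirms how the 0.7 is used. n per arm = 2(1.960 + 0.842)² × 0.7² / 0.176² = 248.3, so 249 against the stated 250. The 0.7 is therefore the SD of a single log10 titre.

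**Formula.** Let Y1 and Y2 be log10 titres at successive visits, bivariate normal with common SD σ. If only subjects with Y1 ≥ c are sampled again,

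E(Y2 | Y1 ≥ c) = μ2 + ρσλ, with a = (c − μ1)/σ and λ = φ(a)/[1 − Φ(a)].

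The reported GMT is the true GMT times 10^(ρσλ).

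**One arm, GMT 32 falling to 16.**

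- Cut-off 1:16: a = (1.204 − 1.505)/0.7 = −0.430; 66.6% kept; λ = 0.546; shift = 0.8 × 0.7 × 0.546 = 0.306; factor 2.02. Reported GMT 32.3 against 16; reported proportion at or above 1:16 is 69% against 50%.
- Cut-off 1:4: a = −1.290; 90% kept; λ = 0.193; shift 0.108; factor 1.28. Reported GMT 20.5 against 16.
- Cut-off 1:16 with ρ from 0.5 to 0.9: reported GMT 25 to 35.

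**Two arms, 64 falling to 32 and 32 falling to 16; true ratio 2.0.**

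- Cut-off 1:16: factors 1.555 and 2.021; ratio 2.0 × 1.555/2.021 = 1.54, with 81% and 67% kept.
- Cut-off 1:4: factors 1.130 and 1.282; ratio 1.76.

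**If the stop is repeated at every visit.** This was simulated with 500,000 subjects per scenario and SD 0.7. Assumed: day-28 GMT 60 or 150; falls of 1.5, 2.5, 3.5 and 5-fold by 3, 6, 9 and 12 months; correlation 0.6 or 0.8. Reported GMT divided by true GMT:

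| Cut-off | 3 months | 12 months |
|---|---|---|
| 1:4 | 1.03–1.14 | 1.25–1.70 |
| 1:16 | 1.17–1.59 | 1.95–3.38 |
| 1:32 | 1.34–2.07 | 2.70–5.25 |

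With correlation 0.7 and a true arm ratio of 2.5 throughout, the reported 12-month ratio is 1.89, 1.57 and 1.47 for the three cut-offs.

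**Two possible repairs, one-arm case with cut-off 1:16.**

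- Entering stopped subjects at an assumed assay floor of 1:2: 0.666 × log10(32.3) + 0.334 × log10(2) = 1.107, a GMT of 12.8 against 16. The bias changes sign, because about 11% of those stopped would be at or above 1:16 at the next visit.
- Using the titres that triggered the stop: kept subjects have an earlier GMT of 77.1 against 32 for everyone. Selecting on Y1 leaves the regression of Y2 on Y1 intact, so log10(32.3) − 0.8 × [log10(77.1) − log10(32)] = 1.510 − 0.306 = 1.204, a GMT of 16.0. The true value is recovered.

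**The case against.** **The unit is not stated.** Note 2 speaks of the antibody level and names no subject, and it sits under a table whose rows are cohort-by-arm groups. A reader might infer that persistence will certainly be computed on good responders only; the text does not support that without condition. This objection stands, and the selection argument is confined to the per-subject reading. The group reading does not rescue the note, since it removes time points and the comparison.

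**The protocol may not intend the stop to operate.** Every other statement schedules draws from all subjects. Section 7.7 (Study Duration) lists sample testing as one block of about a month, and section 9 mentions only the day-28 results. No visit-by-visit return of individual titres is described, so the accumulating 12-month figures rest on an assumption. That is fair, but it is a reason to remove the note rather than leave the contradiction standing.

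**Faster waning.** A reader might infer that the arm that wanes faster is inflated more. With a single stop that is not so: two arms both at 64, falling to 16 and to 32, are each inflated 1.56-fold at cut-off 1:16, and the ratio of 2.0 is preserved. What matters is the level at the deciding visit. Waning rate enters only if the stop is repeated. Nor is decline understated in every sense: within retained subjects it runs from 77 to 32, 2.4-fold against a true 2.0.

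**The size is assumed.** Only the SD comes from the protocol, where it supports the post-booster GMT comparison. At cut-off 1:4 the effect is modest at first.

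**Persistence is secondary.** It does not enter the hypotheses or the sample size. Because no deciding visit is given, a low day-14 result could literally halt the day-28 draw, but nothing shows that this is intended.

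**Conclusion.** The point holds in this form. Note 2 is an undefined, outcome-dependent stop that contradicts the sampling schedule elsewhere in the protocol.

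Applied per subject, with the IPS and no imputation as written, it overstates the 3 to 12 month GMTs and threshold proportions, more so in the arm with lower titres at the deciding visit. The direction follows from the rule, given positively correlated titres; the size depends on the cut-off the protocol does not state. Under the one-step assumptions a GMT of 16 is reported as 20 to 32, and an arm ratio of 2.0 as 1.76 (cut-off 1:4) or 1.54 (cut-off 1:16). Repeated stopping makes it worse by 12 months.

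Applied per group, it loses the weaker group's later time points and the between-arm comparison.

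The documents do not establish which reading is meant. The sample size and the non-inferiority hypotheses are not called into question. The IPS at 18 and 24 months is a separate inconsistency with a schedule that ends at 12 months, and adds nothing to the argument above.

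**What to change.** Delete Note 2 under Table 1 in the synopsis and in section 4.2, so that every subject is sampled at every scheduled time point, as sections 4.2 and 7.4 and Table 4 already provide. The cost is a wording change and the draws the note would have saved, all of which are already scheduled. It should be done before the later visits take place.

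If a stop is kept:

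- State its cut-off, assay, deciding visit and unit, and reconcile the all-subject statements with it.
- For a per-subject stop, analyse persistence with a likelihood-based repeated-measures model that uses all observed titres, including those that triggered the stop, and derive the threshold proportions consistently with it. Do not enter stopped subjects at the assay floor.
- Recognise that no such model replaces time points at which a whole group was not sampled.

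Separately, remove 18 and 24 months from the IPS definition in section 10.2.
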